### Discontinuation criteria

5.3

Discontinuation means that clinical trials have not been completed as planned and part of them have been stopped halfway. The purpose is to ensure the interests of the subjects, protect the quality of the trials, and avoid unnecessary economic losses.

The trial should be discontinued timely if serious safety problems happened.

The trial should be discontinued if the treatment is poor or ineffective, or with no clinical value in order to avoid delaying the effective treatment of the subjects and unnecessary economic loss;

The subject is not willing to continue the clinical trial and drops out halfway;

The subject with allergic reactions or other adverse reaction is supposed to drop out of the trial if researchers think it necessary.

Researchers should keep a record of the reasons subjects drop out in detail.

Automatic withdrawal (subjects who cannot insist on the treatment);Adverse events;Serious complication;Symptoms deteriorate and emergency measures must be taken.

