### Breaking blinding and treatment in emergency

6.3

When serious adverse events happen, researchers should break blindness and take symptomatic treatment immediately.

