### Report on adverse events

6.6

If serious adverse events happen in the trial, the unit undertaking the clinical study should take necessary measures immediately to keep the safety of the subjects and report to the local provincial drug administration and the State Food and Drug Administration (Tel of drug research supervision office of safety supervision department: [name]), the sponsor and the ethics committee in the unit in charge of the study ([contact]), and notify all participating units within 24 hours. The sponsor will ensure to meet all reporting procedures required by laws and regulations.

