### Treatment methods of adverse events

6.7

All the information on serious adverse events should be collected and recorded in the serious adverse events record form. Necessary measures should be taken immediately to ensure the safety of the subjects when each case of adverse events happens, which should be reported to the ethics committee of the Affiliated Hospital of Liaoning University of Traditional Chinese Medicine.

Common adverse reactions in the process of acupuncture include fainting, bent needles, stuck needles, broken needles, and hematoma. When the patient faint during the acupuncture, stop needling immediately, withdraw all the needles, keep the patient lie flat, and pay attention to keep him warm. In mild conditions, patients can recover after lying on his back for a while without the pillow and drinking warm water or with sugar. In serious conditions, besides the above treatment, patients will get acupuncture at Renzhong (GV26), Suliao (DU25), Neiguan (PC6), and Zusanli (TE3) and get moxibustion at Baihui (GV20), Guanyuan (CV4), and Qihai (CV6). If the patient is still unconscious with weak breath and pulse, emergency measures should be taken into consideration.

When the needle is bent, do not withdraw the needle forcibly in case of breaking the needle and leaving it in the body. If the handle is slightly bent, the needle should be withdrawn slowly; if the angle of bending is too large, the needle should be withdrawn along the bending direction. If the bending is caused by the change of the position, the patient should be slowly back to the original position and the needle should be slowly withdrawn after the local muscles are relaxed.

If the needle is stuck, percuss the needle handle or press the muscles near the acupoints of the needle, or insert another needle nearby. If the sticking of the needle is caused by excessive rotation in 1 direction, twist it back in the opposite direction. Scraping or percussing the needle handle also helps to release the twisted muscle fiber.

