The patient cannot change his original position when the needle is broken. If part of the needle body is exposed outside the body, it can be pulled out with fingers or forceps. If the broken end is flat with the skin or slightly sunk, press the skin around the needle vertically with the thumb and the index finger of the left hand until the broken end is exposed, then remove it with forceps held in the right hand. If the broken needle completely penetrates into the subcutaneous or deep muscle layer, it should be located with an X-ray and removed by surgery.

A small part of subcutaneous hemorrhage or local bruises can heal themselves without treatment. If the local swelling and pain are severe, or the bruises affect the daily activity function, stop bleeding with cold compress first and then do hot compress or gently massage in the local area to promote the local blood stasis dissipation and absorption.

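### In 6.7, emergency measures for a patient who stays unconscious after a faint come after acupuncture and moxibustion and are only to be considered, later and weaker than the protocol's own general rule to act immediately

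*Protocol article*

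**What the plan says.** Section 6.7 (Treatment methods of adverse events) opens with a rule for every adverse event: "Necessary measures should be taken immediately to ensure the safety of the subjects when each case of adverse events happens". It then takes the common acupuncture reactions one by one.

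For a faint, the first response is to "stop needling immediately, withdraw all the needles", lay the patient flat and keep him warm. The text then divides by severity. Mild cases rest and drink warm or sugared water. For the others: "In serious conditions, besides the above treatment, patients will get acupuncture at Renzhong (GV26" and at three further points, with moxibustion at three points. The paragraph ends: "If the patient is still unconscious with weak breath and pulse, emergency measures should be taken into consideration".

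Two other sections set general rules for serious adverse events. Section 6.3 says: "When serious adverse events happen, researchers should break blindness and take symptomatic treatment immediately". Section 6.6 says that the unit running the study "should take necessary measures immediately to keep the safety of the subjects". Section 6.4.2 counts immediate danger to life among the criteria for a serious adverse event.

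**The concern.** The fainting paragraph is the only place in the article that tells staff what to do, and in what order, when a participant faints. For the gravest state it describes, it places emergency care after two traditional treatments and asks only that such care be considered. If staff follow the printed order, emergency care could be delayed for a patient who may be in immediate danger.

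The setting adds some weight. Participants are within 3 months of a cerebral infarction or haemorrhage and have a modified Barthel index below 70 (3.3), and the Introduction describes stroke as prone to recur. Loss of consciousness during a session may therefore not be a simple needle faint. Needles stay in place during training led by physical therapists (4.1), so a clear printed trigger would be useful.

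**Working it through.** No calculation applies. The point rests on the order and strength of the wording, so the check sets the texts side by side.

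**1. Order within the fainting paragraph.** Mild and serious are alternative branches by severity. They are not successive steps. The path for a serious case is therefore:

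- (a) stop needling, withdraw the needles, lay the patient flat, keep him warm;
- (b) acupuncture at four points and moxibustion at three;
- (c) emergency measures, if the patient has not recovered consciousness and breath and pulse are weak.

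Emergency measures come last, with one treatment stage between them and the first response. The word *still* in the trigger refers back to what has already been done. The ordinary reading is that (c) arises once (b) has not worked.

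**2. Strength and timing.**

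| Place | Applies to | Action | Timing word |
|---|---|---|---|
| 6.7, opening | each adverse event | necessary measures | immediately |
| 6.3 | serious adverse events | symptomatic treatment | immediately |
| 6.6 | serious adverse events | necessary measures | immediately |
| 6.7, fainting, first response | any faint | stop needling | immediately |
| 6.7, fainting, last sentence | no recovery, weak breath and pulse | emergency measures, to be considered | none |

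The last row describes the gravest patient in the table. It is the only row without a timing word and the only one that asks for consideration instead of action.

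**3. Do the general clauses reach this patient?** The opening of 6.7 covers every adverse event, so it does. Sections 6.3 and 6.6 apply if the event is serious. Under 6.4.2 an unconscious patient with weak breath and pulse can reasonably be judged to be in immediate danger to life, so they probably apply too.

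**4. Do the general clauses repair the order?** They do not. They speak of necessary measures and symptomatic treatment without saying what these are for a faint or which comes first. Someone who starts acupuncture at once could believe that the general rule has been met. The result is a tension between a general rule and a specific one, not a word-for-word contradiction.

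**5. The point code.** In the acupuncture step, 6.7 prints Zusanli with the code TE3. Section 4.2 gives Zusanli as ST36 and assigns TE3 to Zhongzhu. In 6.7 the name and the code therefore identify different points. This slip has no bearing on the order of emergency care. It is noted because it stands in the same paragraph.

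**The case against.** The strongest reply is that the general clauses already cover the case. The fainting paragraph stands under the opening rule of 6.7, nothing in it forbids earlier emergency care, and its first step is itself immediate. All of that is right, and it lowers the risk. It does not remove the point, because the event-specific text is what staff would turn to when a patient faints, and that text points to a later and weaker response.

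A second reply is that the weak verb is loose translation. The English is rough throughout, so this may be part of the explanation. It does not account for the position of the sentence or for the word *still*. Nor should firmer wording elsewhere be leaned on heavily. In 5.3 the phrase "Symptoms deteriorate and emergency measures must be taken" is an item in a list of reasons for withdrawal and does not instruct staff. For a deeply broken needle, 6.7 says that "it should be located with an X-ray and removed by surgery", which names an action but uses the same *should*.

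A third reply is that a standard operating procedure, mentioned in 3.6 but not shown, may give the emergency detail. It may. The point concerns what the protocol prints, not something it omits.

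A reader might also infer more than the text supports:

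- *Every listed point must be treated before emergency care may start.* The text does not say so, and it does not address a patient who shows these signs from the outset.
- *Emergency care is the fourth of four successive steps.* This counts the mild branch, which an unconscious patient does not pass through.
- *The number of planned sessions measures the risk.* The documents give no rate of faints that reach this stage, so a session count has nothing to multiply.

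**Conclusion.** The point holds as a matter of participant safety. The fainting paragraph places emergency measures after acupuncture and moxibustion and asks only that they be considered, which is later and weaker than the protocol's own requirement to act immediately. If followed as printed, the order is unsafe. The general clauses reduce the risk without correcting it.

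Its size is one sentence in one paragraph. No event rate, delay or count of affected participants is claimed, and such events may be very few. Outcomes, analysis and sample size are untouched.

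The conclusion rests on two readings: that *still* refers back to the preceding treatments, and that staff would use the event-specific instruction when a patient faints. That 6.3 and 6.6 also apply depends on a judgement, under 6.4.2, that the state is life-threatening. The opening rule of 6.7 applies without it.

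**What to change.** Replace the last sentence of the fainting paragraph in 6.7 with:

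*If the patient is unconscious with weak breath and pulse at any time, emergency measures start immediately and are not delayed by acupuncture or moxibustion.*

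The existing steps remain for faints without these signs. Two further changes might suggest themselves and are not proposed. One is to let either weak breath or weak pulse trigger the step. The other is to class every such faint automatically as a serious adverse event. Both are clinical decisions that the documents do not settle, and the second would bring the 24-hour reporting duties of 6.6. Whether an event is serious stays with the definition in 6.4.2.

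In the same amendment, change the code after Zusanli in 6.7 from TE3 to ST36, in line with 4.2.

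The cost is one short amendment, covering one sentence and one point code, with the ethics committee approval that 3.5 requires for any modification. It needs no extra staff, visits or participants.

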## Key technology

7

Eye-acupuncture combined with rehabilitation training therapy is aimed at the dysfunction in patients in the convalescent stage of stroke. In order to improve the limb motor function and activity of daily living, different eye-acupuncture regions are selected based on corresponding TCM syndrome differentiation and the stage of stroke, which is the key to the technology. Eye-acupuncture requires skillful manipulation and strict disinfection. When combining eye-acupuncture with physical therapy and occupational therapy, needles are not allowed to fall out in case of bleeding in eye-acupuncture regions around the eyes. The key to ensuring the curative effect of eye-acupuncture combined with rehabilitation training therapy is to establish the normalized operation of eye-acupuncture and rehabilitation training.
